## ANALYSIS PLAN

The primary analyses will be done by comparing the proportions (F-tests) and means (ANOVA) between the intervention townships and the control townships, separately for each intervention. Not only the point estimates but also estimates of variances will be reported as 95% confidence intervals. We will compare the post-intervention differences in the outcomes between the intervention group and the control group. In addition, we will also evaluate the differences between pre-and-post intervention levels for both the intervention and control group to see if the net differences between the 2 groups are statistically significant.

All analyses will include adjustment for the clustering effect and will be done according to the principle of intention to treat.

In both interventions, the main treatment effect will be assumed to be a fixed effect, while the clusters will be assumed to be random. If there are significant differences in the treatment effect among the clusters, either at a cluster level or an individual level, on any of the baseline characteristics, a multilevel modeling approach will be undertaken.

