### Baseline and follow-up surveys

A baseline and a follow-up random sample survey (2 independent samples) of older adults (50+/60+) will be conducted in all of the 120 villages before and after the interventions. In each village, the survey will collect data from 40 consenting adults, half men and half women. Sampling will be done by the China International Center for Chronic Disease Prevention located in Beijing acoording to village rosters collected before the survey. All age-eligible (50+/60+) villagers will receive a random number. The random numbers will be ranked according to ascending order and informed consents will be sought according to the rank orders until 20 men and 20 women in each village consent to participate in the survey. Efforts to make sure that only one older adult from the same household will be recruited in the survey will be made – through a roster including household information or someone (e.g. village chief) who knows the villagers well enough to identify adults from the same household. Blood pressure, weight, height and heart rate will be measured and recorded according to standardized protocol. A brief questionnaire (see Appendix 2) will be administered by survey staff to collect information on disease history, medication use, care seeking patterns, and lifestyle factors. Survey participants will receive a small gift valued at approximately 5 yuan (RMB) as a token of appreciation for their participation in the survey. Five yuan is approximately half of the minimal wage per hour for hourly workers.

High-risk patients in the evaluation surveys will be defined slightly differently from the high-risk definition in the package. It will be defined as having history of heart disease or stroke; or older age (50+/60+) and having diabetes; or older age (50+/60+) and having a measured systolic blood pressure > 160 mmHg; or older age (50+/60+) and currently on anti-hypertension medication but having ever had a self-reported BP measurement > 160 mmHg. See Appendix 2 for details on identification of high-risk patients from the random sample of older adults.

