## APPENDIX 2 – Questionnaire for baseline and follow-up population surveys

**CRHI Survey Questionnaire（2010）**

Hello! My name is . I am a healthcare researcher from (institution). For the purpose of improving health care in your area, we are conducting a health survey to collect information from middle aged or older people in your village. All information collected from this survey will be kept confidential. You are entirely free to decide whether or not to take part in this research study, and there will not be any negative effect to you if you choose not to take part. You are also free to discontinue your involvement with the research study at any time. Thank you for your support and cooperation!

Date (2010/mm/dd) **2010/□□/□□**

Time (hour: minutes) **□□:□□**

| **A. General information** | | | | | | | | | | | | | |
| --- | --- | --- | --- | --- | --- | --- | --- | --- | --- | --- | --- | --- | --- |
| A.1 Name:  A.2 Sex: □1.Male □0.Female  A.3 ID**□□□□□□□□□□□□□□□□□□**  A.4 Years of age  A.5 Years of schooling | | | | | | | | | | | | | |
| **B. Lifestyle information** | | | | | | | | | | | | | |
| B.1 Have you smoked during the past 3 months? (multiple choice)  □1.Yes, cigarette B.1.1 On average, how many cigarettes per day  □2.Yes, tobacco leaf B.1.2 On average, how much “Liang” per day  □3.Other (go to B.2)  □4 No (go to B.2) | | | | | | | | | | | | | |
| B.2 Have you drunk alcohol during the past 3 months? (multiple choice) | | | | | | | | | | | | | |
| □1. Chinese white wine | | | □2. Beer | | | | | | | □0. No  (go to B.3) | | | □3.Other  (go to B. 3) |
| B.2.1How often?  □1. <Once/week  □2. 1-2times/week  □3. 3-5times/week  □4. 1-2times/day  □5. >Twice/day | B.2.2 How much per tima?  □1.<１Liang  □2.1-3 Liang  □3.3-5 Liang  □4.>halt Jin  (note:1Liang=50g≈50ml ;1 Jin=500g≈0.5L) | | B.2.4 How often?  □1. <Once/week  □2.1-2times/week  □3.3-5times/week  □4. 1-2times/day  □5. >Twice/day | | | | | B.2.5 How much per time?  □1.<1bottle  □2.2-5bottles  □3.6-10bottles  □4.>10bottles  (1 bottles=750ml) | |  | | | |
| B.2.3 How many times did you drink alcohol more than half Jin? | | | B.2.6 How many times did you drink alcohol more than 10 bottles? | | | | | | |

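### The primary comparison of mean systolic pressure uses no individual covariates, although age and sex are recorded for everyone; prespecifying both would add modest precision, mainly for the package

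*Protocol*

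**What the plan says.** The Analysis Plan section of the protocol describes the primary analyses as "comparing the proportions (F-tests) and means (ANOVA) between the intervention townships and the control townships", separately for each intervention. The main contrast is after the intervention: "We will compare the post-intervention differences in the outcomes between the intervention group and the control group". A net pre-post comparison is added to it. Clustering is dealt with explicitly: "All analyses will include adjustment for the clustering effect and will be done according to the principle of intention to treat", and "the main treatment effect will be assumed to be a fixed effect, while the clusters will be assumed to be random". A multilevel model is held in reserve under a condition that opens "If there are significant differences in the treatment effect among the clusters, either at a cluster level or an individual level". No individual covariate is named.

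Under Baseline and follow-up surveys, the two surveys are independent random samples of men aged 50 or over and women aged 60 or over. Villagers are approached in random-number order "until 20 men and 20 women in each village consent to participate in the survey". There is no quota or upper limit for age. Section A of the questionnaire in Appendix 2 records sex (item A.2) and age ("A.4 Years of age") for every respondent. Under Statistical Power, about 8 of the 40 respondents per village are expected to be high-risk. They supply the package's primary outcome; all 40 supply the salt outcome.

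**The concern.** Systolic pressure can be expected to vary with age, and perhaps with sex. The survey records both for everyone, and neither intervention can alter them, so adjusting for them is safe. The stated primary model uses neither, and its condition for a richer model concerns variation in the treatment effect, so a difference in age mix between arms would not trigger it.

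Three features of the design make the point relevant. The follow-up sample is newly drawn. Age is open-ended. The sex quota binds the 40 respondents but not the high-risk subset, and because the entry age differs by sex, a shift in that subset's sex mix also shifts its age mix.

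What is at stake is mostly precision, and chiefly in the package comparison, which has the fewer respondents per village. A secondary matter is protection against the part of any consent-related imbalance that acts through age, or through sex in the high-risk subset.

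**Working it through.** **Inputs from Statistical Power.** SD 15 mmHg, ICC 0.05, 120 clusters (60 per arm for each intervention), 8 high-risk people or 40 older adults per cluster, difference 2.5 mmHg, alpha 0.05 (taken as two-sided).

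**Variance components.** Total 15² = 225. Between villages 0.05 × 225 = 11.25. Within villages 225 − 11.25 = 213.75.

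**Reproducing the stated power (post-intervention contrast).** SE = √[2 × (11.25 + 213.75/m)/60]; power = Φ(2.5/SE − 1.96).

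- Salt, m = 40: village-mean variance 11.25 + 5.34 = 16.59; SE 0.744; power 91.9%. The stated figure of more than 90% reproduces.
- Package, m = 8: village-mean variance 11.25 + 26.72 = 37.97; SE 1.125; power 60.3%. The stated figure of more than 90% does not reproduce. The most favourable variant tried (one-sided, no clustering) gives 82.6%. That is a separate matter; 60.3% is used here only as the starting point.

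**Effect of adjustment.** Let R² be the share of within-village variance explained by age and sex. The documents give no value; 5-15% is assumed. The proportional fall in variance is (213.75 × R²/m) / (11.25 + 213.75/m).

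| Contrast | R² 5% | R² 15% |
|---|---|---|
| Package, m = 8 | 1.336/37.97 = 3.5% | 4.008/37.97 = 10.6% |
| Salt, m = 40 | 0.267/16.59 = 1.6% | 0.802/16.59 = 4.8% |

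- Package power: SE 1.125 × √0.965 = 1.105 gives 62%; SE 1.125 × √0.894 = 1.064 gives 65%. In terms of villages, 120/0.965 = 124 and 120/0.894 = 134.
- Salt power: SE 0.744 × √0.984 = 0.738 gives 92%; SE 0.744 × √0.952 = 0.726 gives 93%. These are upper limits. With 20 men and 20 women in every village, sex adds nothing to the variance of the contrast, so only age's share of R² counts.

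**Cross-check from an assumed slope.** Take an age SD of 8 years (range 6-10) and 0.5 mmHg per year (range 0.3-0.8). Then R² = (0.5 × 8/15)² = 7.1% (range 1-28%). Applied to the whole variance, between villages as well as within, which is the more generous treatment, package power is about 64% (range 61-75%) and salt power about 94% (range 92-98%).

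**Chance age differences.** On the same assumptions, with an age ICC of 0.02, the SE of the between-arm difference in mean age is 0.55 years for the package and 0.31 for salt. The 95% range is worth ±0.54 mmHg for the package (1.96 × 0.5 × 0.55) and ±0.30 mmHg for salt. These are components of the standard errors above and do not add to them.

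**If consent did differ by arm.** A 2-year gap in mean age would move the estimate by 2 × 0.5 = 1.0 mmHg (range 0.6-1.6), and the confidence interval would not allow for it. This is illustrative only.

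**The case against.** The strongest objection is that covariate lists normally belong in a statistical analysis plan, which is not available here, and that a cluster-adjusted comparison without covariates is valid under randomization. The second half stands in full: nothing in the Analysis Plan is incorrect. The first half stands in part. The protocol does more than stay silent, since it names a primary method and the condition for going beyond it, so the change improves a stated method.

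That condition also mentions baseline characteristics, and someone might take it as covering imbalance in age. As written, its subject is the treatment effect. Even on the looser reading, the richer model would depend on a significance test.

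A reader might infer more than the documents support:

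- That the ANOVA ignores clustering. It does not.
- That chance age differences bias the results. They do not; the standard error already includes them.
- That the arms will differ in age because of consent. Assessors can learn the allocation and refusers are replaced, so it is possible. But sampling is central, from rosters collected beforehand and in random order, and no document shows differential consent. A net pre-post comparison would also cancel age differences that persist across both surveys.
- That sex can be unbalanced in the salt comparison. The quota rules this out.

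One further objection holds: the high-risk subset is partly selected on systolic pressure itself, which tends to weaken the relation with age. The assumed 5-15% may therefore be too high for the package, where the gain is largest.

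**Conclusion.** The point holds as a modest, inexpensive improvement. It does not show an error or a bias. On the protocol's own SD and ICC and an assumed R² of 5-15%, the variance of the package contrast falls by about 3.5-10.6% and power moves from about 60% to 62-65%; the gain may be smaller because of how the subset is selected. For salt the fall is at most 1.6-4.8%, from age alone. The adjustment would not bring the package comparison to its stated power. It would remove the part of any consent-related imbalance that runs through age, or through sex in the high-risk subset, and would leave other routes untouched. The R² and slope values are assumptions, so the ranges matter more than any single figure.

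**What to change.** In the Analysis Plan, state that the primary mixed model of systolic pressure for each intervention includes the respondent's age (continuous) and sex as prespecified fixed covariates alongside the random cluster effect, and that the unadjusted estimate is reported beside it. Settle this before the follow-up data are seen, so that covariates are not chosen afterwards. Expect a precision gain from sex only in the package comparison. A table of age and sex by arm for the follow-up samples, with response rates, would let readers judge whether consent differed.

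The cost is analysis wording. Both variables are already on the questionnaire, so no new data or fieldwork is needed.

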## STATISTICAL POWER

The sample size has been estimated to provide good statistical power (alpha=0.05, beta=0.90) to detect plausible effects of each intervention. Common assumptions of both sets of power calculations are: 120 clusters, equal randomization between intervention and control and an intra-cluster correlation coefficient of 0.05. These power calculations also assume that there is no interaction between the effects of the package and the effects of salt reduction.

- For the detection of the effects of the package, it is assumed that 8 high risk individuals (20%) will be identified from the 40 survey participants in each cluster, a total of 960 high-risk patients in 120 clusters. Assuming a standard deviation of systolic blood pressure of 15 mmHg, the power to detect a 2.5 mmHg net difference in systolic blood pressure between the intervention and control group pre-post differences will be > 90%. Assuming about half of the high-risk patients will be managed by the village doctors and no difference for those not managed, a 2.5 mmHg difference means a 5 mmHg difference in those actively managed by village doctors. Previous clinical trials demonstrated that even just single drug treatment can lower systolic blood pressure by at least 10 mmHg on average, our targeted blood pressure lowering strategy in package intervention should produce even larger effect. In addition, our CSSS study showed that a low sodium salt substitute could reduce systolic blood pressure by 5.4 mmHg on average. We have reasons to believe that an effect equal or even larger than 5 mmHg systolic blood pressure difference is highly achievable. On the other hand, to achieve a difference smaller than 5 mmHg in systolic blood pressure among those actively managed is not considered meaningful in terms of policy implications. In other words, a smaller effect size is usually not regarded by policy makers as convincing enough for national policies.
- For the detection of the effects of the salt reduction program, assuming a standard deviation of systolic blood pressure of 15 mmHg, the power to detect a 2.5 mmHg net difference in systolic blood pressure between the intervention and control group pre-post differences will be > 90% for a total of 4,800 older adults in the 120 clusters (40 per cluster).

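### The post-intervention comparison ignores the village baseline blood pressure and the net pre-post comparison subtracts it at full weight; adjusting for the village baseline mean would be at least as efficient as either

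*Protocol*

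**What the plan says.** Under Baseline and follow-up surveys, the protocol states "A baseline and a follow-up random sample survey (2 independent samples) of older adults (50+/60+) will be conducted in all of the 120 villages". Each survey takes 40 people per village, so the follow-up people are linked to the baseline people only through their village.

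The Analysis Plan names ANOVA for the comparison of means, run separately for each intervention and adjusted for clustering. It then gives two contrasts. The first is "We will compare the post-intervention differences in the outcomes between the intervention group and the control group". The second is introduced as an addition: "we will also evaluate the differences between pre-and-post intervention levels for both the intervention and control group", to test the net difference. Neither includes baseline blood pressure as a covariate. A multilevel model is mentioned only if treatment effects turn out to vary among clusters, and no baseline outcome term is named for it.

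Statistical Power states its claim for the net contrast, in the same words for each intervention: "the power to detect a 2.5 mmHg net difference in systolic blood pressure between the intervention and control group pre-post differences will be > 90" per cent.

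**The concern.** A village's baseline mean systolic pressure is the same outcome, measured in the same randomised unit before the intervention starts. If village levels persist over the two years, it predicts the follow-up mean and can remove part of the between-village noise.

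The two planned contrasts use it in the two extreme ways. The post-intervention comparison gives it weight 0. The net difference gives it weight 1. Because the samples are independent, the baseline mean carries its own sampling error, and full subtraction passes all of that error into the estimate. The best weight lies between the two, and a covariate model estimates it from the data.

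At stake is precision, not validity. Both planned contrasts are unbiased under the randomisation, but both primary confidence intervals may be wider than the collected data require.

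**Working it through.** **Inputs from Statistical Power.** "good statistical power (alpha=0.05, beta=0.90) to detect plausible effects of each intervention" (beta=0.90 is read as power 0.90, and a two-sided test is assumed); "120 clusters, equal randomization between intervention and control and an intra-cluster correlation coefficient of 0.05"; SD 15 mmHg; effect 2.5 mmHg. Package: "8 high risk individuals (20%) will be identified from the 40 survey participants in each cluster, a total of 960 high-risk patients in 120 clusters". Salt: "for a total of 4,800 older adults in the 120 clusters (40 per cluster").

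**Input not in the protocol.** The correlation of a village's true mean between the two surveys (the cluster autocorrelation, CAC) is an assumption, shown over its range from 0 to 1.

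**Variance of a village mean.** The between-village variance is 225 × 0.05 = 11.25 and the within-village variance is 225 × 0.95 = 213.75.
- Salt, 40 per village: 11.25 + 213.75/40 = 16.59
- Package, 8 per village: 11.25 + 213.75/8 = 37.97
- Baseline mean of all 40 adults: 16.59

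**The plan's own figure first (post-only).** SE = √(2V/60), with power from the noncentral t on 118 df.
- Salt: SE 0.744, power 91.5%. The stated power above 90% reproduces for a post-only contrast.
- Package: SE 1.125, power 59.6%. The stated figure does not reproduce.

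**Net difference.** With the same number surveyed each time, the variance is 2 × (V − CAC × 11.25).
- It beats post-only only when CAC exceeds V/(2 × 11.25). For salt that is 16.59/22.5 = 0.74. For the package it is 37.97/22.5 = 1.69, which cannot occur, so there the net difference always has lower power than ignoring the baseline.
- For salt, power reaches 90% only at a CAC of about 0.7 (90.2%).

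**Adjusted for the village baseline mean of all 40 adults.** ρ = CAC × 11.25/√(V × 16.59), the variance is V × (1 − ρ²), and there are 117 df. For salt the best weight on the baseline is CAC × 11.25/16.59. That is 0.54 at CAC 0.8 and at most 0.68, so a weight of 1 is always too large. For the package this step assumes that high-risk adults share the village effect of all older adults.

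| CAC | Salt: net difference | Salt: adjusted | Package: net difference | Package: adjusted |
|---|---|---|---|---|
| 0 | 65.5% | 91.5% | 34.4% | 59.6% |
| 0.3 | 75.2% | 92.6% | 37.2% | 60.4% |
| 0.5 | 82.6% | 94.3% | 39.3% | 61.8% |
| 0.8 | 93.6% | 97.8% | 43.0% | 65.6% |
| 1 | 98.6% | 99.5% | 45.9% | 69.3% |

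Post-only is 91.5% (salt) and 59.6% (package) in every row. The package net difference uses the baseline of the 8 high-risk adults.

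**Worked row, CAC 0.8.**
- Salt: ρ = 9/16.59 = 0.542 and ρ² = 0.294. The variance falls by 29% to 11.71 and the SE to 0.625.
- Package: ρ = 9/√(37.97 × 16.59) = 0.359 and ρ² = 0.129. The variance falls by 13% to 33.09 and the SE to 1.050.
- Package with the 8-person baseline mean as covariate: ρ = 9/37.97 = 0.237, power 62.1%.

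**Simulation.** Cluster-level runs (4,000 per setting) at CAC 0.8 gave 91.5%, 94.4% and 97.7% for salt (post-only, net, adjusted). For the package with the 8-person baseline they gave 59.2%, 43.3% and 62.1%. With the 40-adult covariate the adjusted package figure was 64.8%.

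**If block terms are also fitted.** Suppose the 30 geographic blocks (10 counties × 3) absorb half of the between-village variance, leaving 5.625. The village-mean variances become 10.97 (salt) and 32.34 (package). If the remaining village effect still has CAC 0.8, adjustment moves salt from 98.3% to 99.4% and the package from 66.3% to 68.9%. If the blocks absorb the stable part, the residual CAC is 0.6 and the figures are 99.0% and 67.7%.

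**The case against.** The strongest reply is that covariates belong in a statistical analysis plan, which may exist and is not at hand. The Analysis Plan section is an outline, it rules out no covariate, and an unadjusted cluster comparison is valid. That is right about validity, and the absence of a covariate list alone would not be a finding. But the protocol does name its primary method and both contrasts, and it ties its power claim to the net difference. The point concerns those stated choices.

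Second, the size depends on a correlation that the protocol does not give. The people differ and the surveys are about two years apart, so low values cannot be excluded. This stands: at CAC 0.3 the gain over post-only is about 1 point for salt and under 1 for the package, and at 0 there is none.

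Third, the package gain leans on high-risk adults sharing the village effect of all older adults. They are selected partly on systolic pressure and disease history, so this is unverified. It also stands. With the 8-person baseline mean instead, the gain at CAC 0.8 is 2.5 points.

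Two stronger readings do not hold. A reader might infer that the plan discards the baseline altogether. It does not: the net difference uses it, and for salt beats post-only once CAC exceeds about 0.74. A reader might also set the adjusted package figure at CAC 0.8 (65.6%) against the net difference (43.0%) and claim about 23 points. That compares a 40-adult covariate with an 8-person subtraction, and with the contrast that the Analysis Plan lists second. Like for like, with 8 people in both, it is 62.1% against 43.0%, and the gain over post-only is far smaller.

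**Conclusion.** The point holds as a modest improvement in efficiency. In large samples the adjusted comparison has a variance no higher than either planned contrast at any CAC, and at CAC 0 the loss is one degree of freedom (salt power stays at 91.5%).

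Over post-only, the gain for salt is 0 to 8 points across CAC 0 to 1, about 3 at 0.5 and 6 at 0.8. For the package it is 0 to 10 points, about 2 at 0.5 and 6 at 0.8, if the village effect is shared. With block terms fitted, the further gain at CAC 0.8 is about 1 point for salt and 2.5 for the package.

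A reader might infer that adjustment rescues the package's power claim. It does not: even at CAC 1 the package reaches only 69.3%, against a stated figure above 90%. That shortfall is a separate matter.

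These results rest on SD 15, ICC 0.05, 60 villages per side for each intervention, equal village sizes and a two-sided 5% test.

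**What to change.** In the Analysis Plan, make the primary model for each intervention a comparison of follow-up systolic pressure with random village effects, adjusted for the village's baseline mean systolic pressure from all 40 surveyed adults as a fixed covariate. Use the same covariate for both primary outcomes. For the package, the 40-adult mean is less noisy than the mean of about 8 high-risk adults. Report the unadjusted post-intervention difference and the net pre-post difference as supportive.

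The cost is a sentence or two of wording and one degree of freedom. No data are added, since the baseline survey is already planned in every village. The change should be fixed before follow-up data are seen.

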## OUTCOMES

The primary outcomes will be the same for the package intervention and the salt reduction intervention, which is the mean blood pressure changes between the groups..

The primary outcome for the package intervention will be mean blood pressure level of high-risk patients.

The primary outcome for the salt reduction intervention will be mean blood pressure level of older adults (50+/60+).

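### The protocol does not fix one primary comparison: post-intervention level and net pre-post difference are both offered, with different power, and a significance test can change the model

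*Protocol*

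**What the plan says.** **OUTCOMES.** One primary outcome is announced for both interventions, "which is the mean blood pressure changes between the groups". The next lines define it as a level: "The primary outcome for the package intervention will be mean blood pressure level of high-risk patients", and likewise the mean level in older adults for salt reduction. Systolic pressure is not named there.

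**STATISTICAL POWER.** For each intervention, power above 90% is claimed for a 2.5 mmHg "net difference in systolic blood pressure between the intervention and control group pre-post differences".

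**ANALYSIS PLAN.** Means are compared by ANOVA, separately for each intervention. Then: "We will compare the post-intervention differences in the outcomes between the intervention group and the control group". Then: "In addition, we will also evaluate the differences between pre-and-post intervention levels for both the intervention and control group", the purpose being "to see if the net differences between the 2 groups are statistically significant". All analyses are to adjust for clustering, with treatment fixed and clusters random. A multilevel model follows on a condition: "If there are significant differences in the treatment effect among the clusters, either at a cluster level or an individual level", on any baseline characteristic.

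**Baseline and follow-up surveys.** The two surveys are independent random samples of the same villages, with 40 adults per village each time.

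**The concern.** Three sections describe three quantities (a change, a level, a net pre-post difference), and none says which one decides whether an intervention worked. The powered quantity is the one that the analysis section introduces as an addition. A trial meant to inform national policy could therefore end with two p-values per intervention that disagree, and with no rule written beforehand to choose between them.

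The choice affects precision. People are not paired across surveys, so subtracting the baseline mean brings in the sampling error of a second sample. It removes only the part of the village effect that persists between surveys. With few people per village the added error dominates; with many it may not.

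The conditional multilevel model adds a second open choice. The protocol names no list of characteristics, no test and no threshold, and does not say which result is primary once the condition is met.

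**Working it through.** **Inputs (STATISTICAL POWER).** 120 clusters, 60 against 60 for each intervention; ICC 0.05; SD 15 mmHg; difference 2.5 mmHg; alpha 0.05. Two-sided testing is assumed, as sidedness is not stated. Each village contributes m = 8 high-risk people (package) or m = 40 older adults (salt reduction). The correlation c of the village effect between the two surveys is not given, so the range 0 to 1 is shown.

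**Step 1. Variance of a village mean.** The between-village part is 0.05 × 225 = 11.25 and the within-village part is 213.75, so V = 11.25 + 213.75/m.
- Package: 11.25 + 26.72 = 37.97
- Salt: 11.25 + 5.34 = 16.59

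**Step 2. Correlation of baseline and follow-up village means.** r = c × 11.25 / V.
- Package: 0 to 0.296
- Salt: 0 to 0.678

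**Step 3. Variance relative to the post-only comparison.** The net difference has factor 2(1 − r). A model adjusted for the village baseline mean has factor 1 − r².

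**Step 4. Power.** SE = √(2 × V × factor / 60); power = Φ(2.5/SE − 1.96). For example, package post-only has SE = √(2 × 37.97/60) = 1.125, giving Φ(2.222 − 1.960) = 60.3%.

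| | Variance factor, c = 0 to 1 | Power, c = 0 to 1 |
|---|---|---|
| Package, post-only | 1.0 | 60.3% |
| Package, net difference | 2.0 to 1.41 | 34.9% to 46.5% |
| Package, baseline-adjusted | 1.0 to 0.91 | 60.3% to 64.3% |
| Salt, post-only | 1.0 | 92.0% |
| Salt, net difference | 2.0 to 0.64 | 66.2% to 98.7% |
| Salt, baseline-adjusted | 1.0 to 0.54 | 92.0% to 99.6% |

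**Step 5. Against the protocol's own figure.** The salt claim of more than 90% is met by the post-only comparison (92.0%). As the net difference named in the text, it is met only if c is high: power is 83.2% at c = 0.5 and 94.0% at c = 0.8. The package claim is met by neither comparison with 8 people per village. That shortfall is a separate point.

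**Step 6. Where the net difference is the more precise.** This needs 2(1 − r) < 1, so r > 0.5. The package cannot reach it, since r is at most 0.296. Salt reaches it when c > 0.5/0.678 = 0.74.

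**Step 7. Baseline adjustment against both.** 1 − r² never exceeds 1. Also 1 − r² = (1 − r)(1 + r), which never exceeds 2(1 − r) because 1 + r is at most 2. At planning level its variance is therefore never larger than that of either stated comparison. At c = 0 it equals post-only.

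**Step 8. Two chances at 5%.** Under the null the two test statistics correlate at √((1 − r)/2): 0.707 to 0.593 for the package and 0.707 to 0.401 for salt. In 2 million bivariate normal draws per setting, at least one was significant in 8.3% to 8.8% (package) and 8.3% to 9.3% (salt).

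**The case against.** - **The order implies a choice.** The ANALYSIS PLAN puts the post-intervention comparison first and the net difference second, so post-only could be read as primary. That is a fair reading of the section alone. It does not settle the matter, because the power section is written for the other quantity and OUTCOMES opens with changes. An SAP, not shown here, may settle it; the protocol's sections would still disagree.
- **There is only one effect.** This stands. The expected baseline difference between arms is zero, so both comparisons estimate the same average effect. A reader might infer two competing treatment effects, or a plan to choose after seeing the results. The documents show neither, only that the choice is left open.
- **The net difference may help.** A reader might infer that it is simply the wrong tool. That holds for the package at every c, but not for salt above c of about 0.74.
- **Clustering is handled anyway.** This stands: adjustment is promised in all analyses, so the trigger does not decide whether clustering is respected, and no effect on the primary p-value is shown. Its purpose is then unclear.
- **The trigger might seem impossible or sure to misfire.** Each township has one allocation, so a treatment effect within a township cannot be estimated. The sentence can equally mean effect modification by baseline characteristics, which can. Chance triggering depends on a number of tests that the protocol does not give. With independent tests at 5%, 1 − 0.95^k is 23% for 5, 40% for 10 and 64% for 20. These are chances of a model switch, not of a false-positive trial.
- **Systolic is evidently meant.** Agreed. The power section and the secondary definitions of control and hypertension use systolic pressure. Naming it in OUTCOMES is a wording repair.

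**Conclusion.** The point holds and should be fixed before analysis. The protocol names two candidate primary comparisons and does not rank them consistently across sections. For the package, the choice moves power from 60% down to between 35% and 46.5%. For salt, it moves power from 92% to anywhere between 66% and 99%. Free choice between them would put the false-positive rate per intervention at about 8% to 9% instead of 5%.

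The harm is to precision, power and error control. It is not bias, since both comparisons estimate the same average effect. The model trigger is a lesser fault: a data-dependent step with no clear purpose that leaves open which result is primary.

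The figures rest on the protocol's SD, ICC and cluster sizes, the same ICC in high-risk people as in all older adults, equal village sizes, two-sided testing, a normal approximation, and the assumed 0 to 1 range for c.

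**What to change.** Declare one primary analysis for each intervention:

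- **Outcome:** mean systolic pressure at the follow-up survey, as the average of the two survey readings.
- **Model:** a linear mixed model, fitted unconditionally, with village as random effect.
- **Covariates:** the village's baseline-survey mean systolic pressure in the same population (high-risk people for the package, all older adults for salt reduction), the county and block strata used in RANDOMIZATION, and the other factorial intervention.

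Make the unadjusted post-only and net-difference comparisons supportive. Delete the significance trigger; effect modification by baseline characteristics can be explored as a secondary analysis. Align OUTCOMES, STATISTICAL POWER and ANALYSIS PLAN on this comparison, name systolic pressure in OUTCOMES, and restate power for it with the assumed between-survey correlation shown.

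The cost is protocol wording and one recalculation. Every variable is already collected or known from the randomization. The gain from baseline adjustment is modest for the package (at most 9% of the variance) and possibly large for salt (up to 46%). The main benefit is a single result fixed in advance.
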